## Abstract

**Background:**

Multiple sclerosis is a chronic and disabling neurological disease among young people. One of the major complaints in patients with multiple sclerosis (PWMS) is falling. There are a number of factors that risk factors for falling, including balance disorder and spasticity. Core stability (CS) exercises such as trunk muscle strengthening exercises can improve balance and mobility and reduce falling. Dynamic neuromuscular stabilization (DNS) exercise is a new functional rehabilitation strategy that optimizes motor function based on the principles of developmental kinesiology. This trial will evaluate the effectiveness of DNS in comparison to CS on balance, spasticity, and falling in PWMS.

**Methods:**

A total of 64 PWMS, between 30 and 50 years old and expanded disability status scale (EDSS) between 2 to 5, will be recruited from neurophysiotherapy clinic, Faculty of Rehabilitation Sciences, Iran University of Medical Sciences to participate in this 2-armed parallel study. Participants will be randomly divided into two groups to receive CS exercise or DNS exercise. All participants will receive exercise treatment for 15 sessions during a period of 5 weeks (3 sessions per week). Primary outcome measures will be balance. Falling rate, fear of falling, patient mobility, as well as spasticity, will be measured as secondary outcomes. All outcome measures will be measured at baseline, the day after the completion of the 15th session, and after 17 weeks.

**Discussion:**

Dynamic neurostabilization exercises utilize the subconscious stimulation of special zones to reflexively mediate the diaphragm and other core stabilization muscles, which is extremely effective for individuals with reduced somatosensory or movement awareness. Findings from the proposed study are expected to benefit the knowledge base of the physiotherapist, and it can be a good alternative for the rehabilitation program and even reduce medication use in patients with multiple sclerosis. These exercises are easy to understand and applicable for these patients and their partners as well.

**Trial registration:**

The trial was registered in the Iran registry organization with code IRCT20140222016680N5 and was approved on April 7^th^, 2020. Address: IRCT administration team, [name].

## Background

Multiple sclerosis is a chronic neurological disease and the most important cause of non-traumatic disability among young people [1]. Among the wide range of symptoms associated with multiple sclerosis, falling is one of the major complaints and a symptom experienced by more than 50% of PWMS [2]. Falling causes pain, injury and fracture, and fear of falling [3]. There are a number of risk factors for falling in PWMS, including balance disorders, spasticity, and cognitive impairments [4]. Living environment, using cane, fatigue, decreased muscle endurance, heat sensitivity, and urinary incontinence are the other risk factors for falling in PWMS [5, 6]. Patients who have a falling history walk more slowly and cautiously, and cannot correctly push their feet off the ground [7].

Balance impairment is the most common risk factor for falling in PWMS with any degree of disability [8, 9]. Individuals with multiple sclerosis have different strategies to maintain balance in comparison to healthy individuals [10, 11]. They tend to use more compensatory postural adjustments and fewer anticipatory postural adjustments [12]. Lack of trunk control and limited trunk muscle activities is some of the most important causes of balance disorders in PWMS. These patients have delayed onset times for trunk muscles, which are correlated with poor sitting balance. They have been found to have less trunk stability during arm movements compared to healthy subjects [13]. As a result, they have reduced trunk dissociation between the upper and lower trunk, and between the trunk and lower extremity, which is one of the key factors for postural control impairment [14].

Spasticity is another common disorder in PWMS that leads to falling [15]. Spasticity is said to be an annoying and disruptive factor in patient's daily living [16]. It increases the likelihood of falling by increasing energy consumption, fatigue, and disturbing the patient's sleep [15]. Additionally, spasticity decreases the quality of life and causes pain and disability [16, 17]. According to the Lewit and Ryerson approach, disruption of the muscle length-tension relationship, postural instability, and impairment of muscle activity pattern cause high tonocity in lower limb muscles [18].

Some neurologic disorders rather than multiple sclerosis such as stroke, and cerebellar palsy experience high tonocity in lower limbs. Evidence shows that these patients have less trunk control and, as a result, less capacity for selective lower limb movements [18, 19]. However, studies conducted on trunk control in PWMS are limited. It has been shown that the trunk position affects the biomechanics of the lower extremities [20]. Trunk control is the strongest predictor for gait capacity in lower extremity spasticity [19], and there is a high positive correlation between trunk control and balance in patients with spastic limbs such as cerebral palsy [21].

Various studies have investigated the effect of trunk muscle training on reducing balance disorders and falling in PWMS [22–24]. Core stability (CS) training is a controlled form of exercise using the body stabilizing muscles, with emphasis on the deep abdominal muscles [25]. These muscle groups are thought to contribute to trunk stability and optimal lumbar-pelvic stabilization needed for daily activities [26]. CS training is recommended by international multiple sclerosis association guidelines [27] and has been commonly used for PWMS. Although CS exercises can improve balance and mobility, reduce falling rate and fear of falling in PWMS, they have no emphasis on trunk muscle timing and joint positioning [22–24]. Moreover, the combination of spinal stabilization with a dyaphragmatic breathing pattern has been missed in CS training. Dynamic neuromuscular stabilization (DNS) exercises are a new functional rehabilitation strategy that optimizes motor function based on the principles of developmental kinesiology [28]. It is based on the pattern of human motor development in the early years of life that controls posture, maintains it against gravity, and activates muscles purposefully [29, 30]. One of the most fundamental purposes of the DNS approach is to support joints and all segments into a functionally central position, at timing muscle coordination [29]. In DNS, the individual must maintain the intra-abdominal pressure and perform the locomotive movement voluntarily [28]. According to the evidence, DNS is an effective protocol to significantly improve respiratory function [31], and reduce forward head posture [32]. It was effective in standing, walking, and jumping in patients with spastic diplegic cerebellar palsy [33], and in addition, DNS can improve trunk function, balance, and fear of falling in individuals with hemiparetic stroke [34]. Thus, we hypothesize that by establishing a normal postural alignment and proper trunk muscle activation pattern by DNS in PWMS, balance may be improved and the tone of lower limbs can be reduced. The aim of this study is to determine the effects of DNS exercises on balance, trunk function, falling, and spasticity, and compare them with CS exercises.

## Methods and design

### Trial design

This study is a two parallel armed, parallel groups, superiority randomized controlled trial, compared DNS exercise, to CS exercises in PWMS. This randomized controlled trial is with one to one allocation in two groups (group 1: DNS exercise, group 2: CS exercise). The time schedule of enrolment, interventions, and assessments is presented in Table 1.

**Table 1 Tab1:**
[figure not shown]
Schedule of enrollment, intervention, and assessment of PWMS

### Participants

Women and men with multiple sclerosis aged between 30 and 50 years with moderate disabilities (EDSS between 2 and 5) will be included in the study from June 2020.

### Inclusion and exclusion criteria

Patients with a minimum score of 21 from the mini-mental scale examination, ability to walk, having sustained falling during the last 3 months, and at least high school graduation to fill out self-declaration questionnaires will be eligible. Patients with other neurological disorders, multiple sclerosis exacerbation during the last month, apraxia (due to inability to learn and practice the exercises), severe spasticity (score above three based on modified Ashworth scale), having a history of major surgery in the lower extremities, explicit postural abnormalities in the spine and lower limbs such as scoliosis and kyphosis and cardiovascular disease will be excluded.

### Recruitment procedures

Recruitment will take place in two steps: firstly, patients who were previously confirmed by neurologists for multiple sclerosis are referred to the neuro-physiotherapy clinic, Faculty of Rehabilitation Sciences, Iran University of Medical Sciences. Secondly, the assessor, who is a researcher, will conduct another screening for inclusion and exclusion criteria, will evaluate outcome measures, and make the final decision regarding the eligibility of the patients the same day; patients are referred to the clinic. If eligible, the patient will be provided with oral and written information about the study. Background information including name, contact number, height and weight, medical history, and medications used will be obtained from participants. Having signed a consent form by the treatment provider, patients will be randomized to one of the two treatment groups. and the assessment will be performed the same day of screening, in the physiotherapy evaluation laboratory in the School of Rehabilitation Sciences at the Iran University of Medical Sciences, Tehran.

One or two days later treatment sessions will be started in participants’ houses for 5 weeks (three times a week) by a treatment practitioner who is a physiotherapist with five years of experience in the field of neuro-physiotherapy. Because of the COVID-19 pandemic, all treatment sessions will be held in patient’s houses and the patients will come to physiotherapy evaluation laboratory for three times of assessment (baseline, one or two days after 15th session and 17 weeks after randomization day). All treatment sessions are free for all participants and the cost of any travel to the evaluation laboratory for assessment will be borne by the research team.

### Randomization

The participants, with the permuted block randomization method, will be randomized to dynamic neuromuscular stabilization exercises or core stability exercises by an independent researcher not involved in outcome assessments. Sixteen quadruple blocks will be produced using the site www.sealedenvelope.com. In order to apply concealment in the randomization process, unique codes will be used on the envelopes in which the type of exercises is specified by an analyzer.

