### Implementation

Allocation sequence, participant enrollment, and participant assignment to treatment groups will be performed by an independent person who is not involved in assessments, intervention, and any other part of the research.

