### Blinding

In this study, the assessor who evaluates the outcome of the study will be blind to the allocation of the treatment groups and doesn’t provide intervention. After each assessment session, she will enter all data electronically. It may be done in Rehabilitation Research Center, Department of Physiotherapy, where the data will have gathered. Additionally, the analyzer who is independent from the research team and is blind to participant’s allocation will monitor data of the study after trial termination and analyze data.

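### The protocol contradicts itself on who enrols, takes consent, fills envelopes and stays blind; with every block fixed at four, this puts allocation concealment at risk

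*Protocol article*

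**What the plan says.** Five sections of the protocol article bear on this.

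- **Trial design** sets "one to one allocation in two groups (group 1: DNS exercise, group 2: CS exercise"), so the key from number to arm is public.
- **Randomization** uses permuted blocks of a single size: "Sixteen quadruple blocks will be produced using the site" named there. An independent researcher, excluded only from outcome assessment, randomises. The envelopes carry codes, "in which the type of exercises is specified by an analyzer". **Concealment** repeats that the group number is inside the envelope and calls the analyzer blind.
- **Recruitment procedures** has the assessor screen, evaluate outcome measures and make the final eligibility decision. It continues: "Having signed a consent form by the treatment provider, patients will be randomized to one of the two treatment groups". Sessions start one or two days later and are delivered "by a treatment practitioner who is a physiotherapist with five years of experience in the field of neuro-physiotherapy". Interventions says that the treatment practitioner supervises all 15 sessions.
- **Implementation** says that the sequence, "participant enrollment, and participant assignment to treatment groups will be performed by an independent person who is not involved in assessments, intervention", or any other part of the research.
- **Blinding** describes "the analyzer who is independent from the research team and is blind to" participants' allocation, and has that person analyse the data after the trial ends.

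**The concern.** Two protections are claimed, and the text undermines both.

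The first is concealment. It requires that whoever can influence whether and when a patient enters does not know the next assignment. A therapist who treats both arms sees past allocations. If that therapist also takes consent, and all blocks have the same short length, counting within a block reveals or strongly suggests the next arm. Consent could then be encouraged, discouraged or delayed accordingly. That is selection bias, and randomisation cannot remove it afterwards.

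The second is blinding of the analysis. A person who decides or records which group goes in which coded envelope holds the link between code and arm. Data analysis leaves a choice between regression and a Mann-Whitney test that depends on how the data look, so it matters whether the analyst knows the arms when choosing.

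**Working it through.** **The plan's own figure.** 16 blocks x 4 = 64 = 2 x 32, which agrees with the target of 64 in Trial status and the 32 per group in Sample size calculation. The block count is sound.

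**Roles set side by side**

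| Task | Implementation | Elsewhere |
|---|---|---|
| Eligibility decision | Independent person (as part of enrolment) | Outcome assessor (Recruitment procedures) |
| Consent | Independent person (as part of enrolment) | Treatment provider, on the natural reading (Recruitment procedures) |
| Envelope content | Independent person (as part of sequence and assignment) | An analyzer (Randomization, Concealment) |

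Implementation excludes its independent person from assessment, intervention and every other part of the research. That person therefore cannot be the assessor, the treatment provider or the data analyst. The two right-hand columns cannot both be true.

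**Predictability of a 1:1 block of four.** Assumptions: the observer knows the block size, the block boundaries and all past allocations. There are six equally likely orderings: AABB, ABAB, ABBA, BAAB, BABA, BBAA.

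Certain in advance:
- The fourth assignment is always certain: 1.
- The third is certain when the first two match (AABB, BBAA): 2/6 = 1/3.
- Per block: 1 + 1/3 = 1.333 of 4 = 33.3%. Over 16 blocks: 16 x 1.333 = 21.3 of 64.

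Best guess, choosing the arm with more places left:
- First: 1/2.
- Second: 2/3.
- Third: (1/3 x 1) + (2/3 x 1/2) = 2/3.
- Fourth: 1.
- Per block: 1/2 + 2/3 + 2/3 + 1 = 2.833 of 4 = 70.8%. Over 16 blocks: 16 x 2.833 = 45.3 of 64, against 32 of 64 by chance.

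**What varying the block size achieves.** This is a simulation of 1,500 sequences of 64. The observer knows the set of possible sizes but not which size is in use. The sets are assumptions chosen for illustration.

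| Block sizes | Certain in advance | Best guess correct |
|---|---|---|
| 4 only | 33.3% | 70.8% |
| 2, 4, 6 | about 4% | about 70% |
| 4, 6, 8 | about 2% | about 68% |

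Varying sizes almost removes certainty but hardly changes the guess rate, because favouring the arm that is behind works whatever the block size. The guess rate does harm only if the guesser can act on it, so the effective step is to take consent out of the therapist's hands.

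**Analyst blinding.** Specifying group 1 or 2 inside a uniquely coded envelope means knowing which code has which group. Trial design publishes which number is which exercise, so the number masks nothing. An analyzer who does this is not blind to the envelopes.

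**The case against.** The strongest reply is that the therapist has little room to act. The assessor, not the therapist, decides eligibility; envelopes are coded; an independent person assigns. Certain prediction needs the block size and a careful count, and nothing says that staff are told the size. The consent sentence is badly worded, and the text says treatment provider in one place and treatment practitioner in another. All of this stands as a limit. The therapist's route is consent and its timing only, and the consent reading, though natural, is an inference. It does not remove the point: the article does not say that the size is withheld, it describes one practitioner in the singular for both arms, and the independent person who would protect allocation is contradicted by other sections.

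A reader might also infer three stronger things that the document does not support.

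- **That the data analyst is unblinded.** No sentence says that the envelope analyzer and the data analyzer are the same person. The shared title and the shared description as blind suggest it, but they could be two people.
- **That baseline is measured after randomisation.** The words "and the assessment will be performed the same day of screening" follow the mention of randomisation, but they fix only the day and place. Earlier in the same paragraph the assessor evaluates outcome measures before information, consent and randomisation. The order is ambiguous, no more.
- **That the treatment estimate is biased by some stated amount.** This would need an assumed prognostic difference between patients steered to each arm and an assumed degree of steering. It would also have to allow for the planned baseline adjustment. The document supplies no basis for these assumptions.

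**Conclusion.** The contradiction in roles is plain on the text and must be reconciled. Concealment is at risk, not shown to have failed: 33.3% of assignments (about 21 of 64) would be certain in advance and 70.8% guessable. Both figures are conditional on the consent reading and on a therapist who knows past allocations and knows or infers the block size. Describing the person who specifies envelope contents as blind is contradictory in itself. Whether it also defeats blinding of the analysis depends on whether that person is the data analyst, which the article leaves open. The sample size is unaffected. The changes are cheap and worth making.

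**What to change.** For any enrolment still to come:

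1. Have consent taken by an independent person of the kind Implementation describes, not by the treating therapist. This is the main remedy.
2. Have the list generated and the envelopes filled by such an independent person, not by the data analyst. Whoever holds the list should not also take consent, since that person would know every next assignment; two uninvolved people are preferable to one.
3. Use randomly varying block sizes (for example 2, 4 and 6) not disclosed to clinic staff. Expect certain predictions to fall to about 4%, and best guesses only to about 70%.
4. Give the analyst data labelled A and B, without the code list and not labelled 1 and 2, until the primary analysis is final.
5. Make Recruitment procedures, Randomization, Concealment, Implementation and Blinding agree. Name one role per task, say whether the two analyzers are different people, and state that baseline measures are complete before the envelope is opened.

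The cost is a regenerated remainder of the list, some reassignment of tasks, and a slight imbalance if the final block is incomplete (at most 6/2 = 3 patients with a largest block of six). Enrolment began in June 2020 and the article does not say how much remains. If none does, items 1 to 3 no longer apply, and the report should instead state who actually did each task; items 4 and 5 remain useful.

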### Concealment

For concealment in the randomization process, a unique code will be used on each envelope with the group number (1 or 2) specified inside which will be done by a blind analyzer.

### Implementation

Allocation sequence, participant enrollment, and participant assignment to treatment groups will be performed by an independent person who is not involved in assessments, intervention, and any other part of the research.

### Blinding

In this study, the assessor who evaluates the outcome of the study will be blind to the allocation of the treatment groups and doesn’t provide intervention. After each assessment session, she will enter all data electronically. It may be done in Rehabilitation Research Center, Department of Physiotherapy, where the data will have gathered. Additionally, the analyzer who is independent from the research team and is blind to participant’s allocation will monitor data of the study after trial termination and analyze data.

### Sample size calculation

This study, for the first time, compares DNS exercises with CS exercises in PWMS. Due to the lack of previous studies and considering the main goal of study as comparing two groups the day after the completion of the 15th sessions, the Cohen standardized effect size for comparing means of two independent groups was used in this study to calculate the sample size. Considering the probability of the first type error of 5%, the power of 80%, the standard Cohen’s effect size of 0.8, and using G-Power software the sample size was calculated as 26 subjects in each group which increased to 32 subjects to assume the 20% of dropout rate. Another power calculation will be performed at the end of the trial to assure the sufficiency of the sample size.

### Interventions

At first, necessary explanations about the importance of exercise therapy in PWMS will be given to the participants. In both groups, exercise sessions will be delivered three times a week, over a course of 5 weeks, and the duration of each session will be 60 to 75 min. All 15 sessions will be supervised by the treatment practitioner at the participant’s houses individually due to COVID-19. In addition, the participants or their companions are required to make the home environment as safe as possible to minimize the likelihood of falling.

In two pamphlets, both groups will be given the exercises (DNS and CS) with the description required to do their exercises on days when the treatment practitioner is not present. In order to remind exercises to the participants, a reminder will be set on their cellphones. In addition, the participants will be instructed not to do any other exercises, nor receive other types of physiotherapy treatment during 5 weeks’ treatment sessions. If female participants get pregnant during the treatment plan or any fracture accrued during treatment sessions, they will be excluded.

Four barriers to exercise in PWMS are anticipated. The first is fatigue. Rest intervals are taken between specified exercises depending on one’s condition. Participants will be highly recommended to stop any exercise movement when they feel a lack of energy and any fatigue signs which are important in PWMS will be discontinued treatment sessions. The second is menstruation in women. The treatment session will be canceled on the first day of menstruation. The third is the time of the treatment session. The exercises will be performed in the morning or evening based on the participant’s comfort and level of energy. The fourth is medication. Treatment sessions will take place 48 h after the participant’s multiple sclerosis-related medications.

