### Data analysis

SPSS version 22 will be used for data analysis. We will perform an intention-to-treat analysis for dropout participants during treatment sessions and in follow-up assessment sessions. Conditional mean imputation was performed. Mean (standard deviation) or median (first quartile and third quartile) will be used to describe the quantitative variables according to the distribution of variables, and for categorical variables, frequency (percentages) will be used. Graphical methods, numerical indices, and Shapiro-Wilk’s tests will be used to check the normality of different measures.

To compare quantitative demographic variables between the two groups, an independent *t*-test or nonparametric test, Mann Whitney *U*-test will be used. Chi-squared or Fisher’s tests will be used to compare the categorical demographic variables between the two groups.

A separate regression analysis will be done at each follow-up point (i.e. the day after the completion of the 15th session (T2), and after 17 weeks follow-up (T3) each one including group and baseline (T1) as a covariate. The T2 and T3 follow-up point will be considered primary and secondary, respectively. A non-parametric analysis would be a Mann-Whitney *U*-test of the differences (follow-up minus baseline). A 2-tailed *P* < 0.05 will be considered significant.

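### Excluding randomised patients for pregnancy or a fracture during treatment is not reconciled with the intention-to-treat analysis, and for fracture the removal may be informative

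*Protocol article*

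**What the plan says.** The rule stands in the Interventions section of the protocol article: "If female participants get pregnant during the treatment plan or any fracture accrued during treatment sessions, they will be excluded". Under Recruitment procedures, patients are randomised after consent, and then "One or two days later treatment sessions will be started". Anyone who meets the rule has therefore already been allocated.

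The Data analysis section states: "We will perform an intention-to-treat analysis for dropout participants during treatment sessions and in follow-up assessment sessions". The next sentence gives the missing-data method: "Conditional mean imputation was performed".

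The Background says "Falling causes pain, injury and fracture, and fear of falling". Falling rate, asked of the patient or partner, and fear of falling, by questionnaire, are listed under Secondary outcome measures. The primary outcome is the Berg Balance Scale, with the day after the 15th session (T2) as the primary time point.

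No section says whether a patient excluded under this rule is still assessed at T2 and T3, is still in the analysis set, or still has falls counted.

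**The concern.** Intention-to-treat means that every randomised patient is analysed in the allocated arm, whatever happens afterwards. A rule that takes randomised patients out because of a later event works against that, unless the document says that only the exercises stop.

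Pregnancy and fracture differ here. For pregnancy, the issue is the principle and the loss of randomised patients; nothing in the documents ties it to the outcomes. For fracture there is a possible bias. Every participant must have fallen recently to be eligible, and the article itself links falls to fracture. A fracture in the treatment period is thus likely to mark a poor fall outcome, and may be related to the allocated exercise. If fractures were uneven between arms, the arm with more of them would lose some of its worst fall outcomes, and the comparison of falls and fear of falling would favour it. Data that are never collected cannot be restored at the analysis.

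**Working it through.** **1. Planned size, as the base for the illustration.** Inputs from Sample size calculation and Data analysis: effect size d = 0.8, power 80%, two-sided 5%, 1:1 allocation. The two-sample t-test (noncentral t) gives 25.52, rounded up to 26 per group, as stated. Adding 20% gives 26 × 1.2 = 31.2, rounded up to the stated 32. (Dividing by 0.8 gives 32.5, hence 33; the difference of one patient plays no part here.) The base is 32 per arm.

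**2. What *excluded* most naturally means.**
- Inclusion and exclusion criteria uses the word for patients who are not in the trial at all: "such as scoliosis and kyphosis and cardiovascular disease will be excluded".
- Interventions has other words for interrupting exercise: sessions are discontinued for fatigue and canceled for menstruation. Only pregnancy and fracture lead to exclusion.
- Data analysis speaks of dropouts and does not mention excluded patients.

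The natural reading is removal from the study, but the text does not settle it.

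**3. Consequence under each reading.**
- *Out of the study:* the patient is not assessed at T2 or T3 and is not analysed. This conflicts with intention-to-treat. Falls are counted by asking at assessments, so the fall behind a fracture would go uncounted.
- *Exercises stop and the patient is handled as a dropout:* the patient stays in the analysis through imputation. The missing fall count is replaced by an average predicted from patients who were observed. The formal conflict softens, but the fall that led to the fracture is still replaced by an average.
- *Exercises stop and assessments continue:* no conflict and no loss, but nothing in the article says this.

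**4. Possible size of the shift.** Each removal is 1/32 = 3.1% of an arm. If k of 32 patients in one arm are removed and their outcomes lie g SD below the full-arm mean, the mean of those remaining rises by k × g / (32 − k) SD. Both k and g are assumptions.

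| k removed | g = 1 | g = 1.5 | g = 2 |
|---|---|---|---|
| 1 | 0.032 | 0.048 | 0.065 |
| 2 | 0.067 | 0.100 | 0.133 |
| 3 | 0.103 | 0.155 | 0.207 |

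Against the design effect of 0.8 SD, this runs from 0.032/0.8 = 4% to 0.207/0.8 = 26%. The upper end needs three removals, all in one arm, each 2 SD low.

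**5. Power.** At d = 0.8, power is 88.3% with 32 per arm, 87.3% with 31, 86.1% with 30 and 84.9% with 29. Loss of power is not the problem; selective removal is.

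**The case against.** The strongest reply is that the sentence stands under Interventions, directly after the rules on other exercise and physiotherapy, and so may only end the allocated exercise. It does not mention follow-up or analysis. The intention-to-treat sentence covers patients who drop out in the treatment period and is followed by an imputation method, so these patients could be analysed as dropouts. This stands in part: the contradiction is the natural reading, not the only one. It does not remove the concern about falls, for the reason given in the second reading above.

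The scope is also limited. Read narrowly, the rule covers only fractures within the supervised sessions: at most 15 × 75 min = 1,125 min, or 18.75 hours, delivered one to one. The article also uses similar wording for the whole five weeks, which would take in a fracture from a fall at home. On either reading, injurious falls without fracture and fractures after the treatment period are untouched, and not every fracture need come from a fall. A reader might infer that the plan removes the most serious falls in general; the documents do not support that.

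A reader might also infer that harms would vanish from the report. That rests on silence. Leaving an efficacy analysis does not stop an event from being reported as a harm, and an article commonly leaves harms procedures to the full protocol.

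Finally, the Berg scale is performance-based and cannot be done by telephone. This is correct, and the fix has to allow for it.

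**Conclusion.** The concern holds in a limited form. As written, randomised patients are to be excluded for events after randomisation. That conflicts, on its natural reading, with the stated intention-to-treat analysis, and no text keeps these patients in follow-up or analysis. For fracture the removal may be informative for falling rate and fear of falling; for pregnancy no bias mechanism is shown.

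The effect lies mainly on the fall outcomes and on whether the result can be called intention-to-treat. It would be tempting to conclude that the primary Berg comparison is seriously biased. The documents do not support that: they give no fracture or pregnancy rate and no Berg SD, and events may be few or none. The range of 0.03 to 0.21 SD rests wholly on the assumed 1 to 3 removals in one arm at 1 to 2 SD below its mean.

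This is more than detail left to a fuller document, because the article states a rule that does not fit its own analysis principle.

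**What to change.** Reconcile Interventions and Data analysis by separating two things: stopping the exercises, which is a clinical matter on which no view is taken here, and leaving the study. State that:

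- every randomised patient stays in follow-up and is analysed in the allocated arm, whatever sessions were received;
- T2 and T3 assessments are still sought after a pregnancy or fracture, with questionnaires and fall counts taken by telephone if the patient cannot attend;
- a Berg score that cannot be performed is treated as missing under the stated missing-data method;
- fractures are reported by arm.

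The fall question looks back 6 months, so asking it at T2 or T3 would still cover the treatment period. The cost is a few sentences in the protocol, a few telephone assessments and some missing Berg scores. Enrolment began in June 2020, so for patients already taken out, only what can still be asked is recoverable.
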